**Identification**
Fake medical record number (dummy number to track patients over time without being able to identify them)Fake encounter number (dummy number to track encounter-related data without being able to identify specific encounter)
**Encounter information**
Encounter typeDays since index discharge (we could not use real dates, sites provided us with the number of days since discharge from the index hospitalization for chronic obstructive pulmonary disease (COPD) whereby admission for the index was a negative number [0-day prior to discharge] and all subsequent encounters including ED visits, rehospitalizations, and outpatient visits were a positive number [0 + days until that encounter])Length of stayDischarge location
**Diagnosis codes (for the index COPD hospitalization, specific *International Classification of Diseases, Tenth Revision (ICD-10)* codes were used; for all other encounters we captured all *ICD-10* codes)**
Primary *ICD-10* codeSecondary *ICD-10* codesDiagnostic-related groups (optional)
**Characteristics**
Primary insuranceSecondary insuranceAge at encounterGenderRaceEthnicityFirst 3 digits of zip code
**COPD data (optional)**
Smoking statusDisease durationDisease severityPulmonary rehabilitation referralSmoking cessation referralOutpatient oxygen orderHome health ordered
**Intervention data (tailored to each site whereby primary metric was reach (yes or no) with other metrics decided at the site level)**
Interventions 1, 2, and 3 completedOther metrics for interventions 1, 2, and 3

**Table 3 table3:** Sustainment, fidelity, and cost data collection by end-user group.

End-user group	Sustainment	Fidelity	Cost analysis
Site leads	✓	✓	✓
Organizational leaders	✓		
Clinicians	✓	✓	
Patients and caregivers	✓		

**Table 4 table4:** Sustainment, fidelity, and cost domains.

Domain	Focus	End-user group	Data collection methods
Sustainment	Extent to which transitions of care (TOC) interventions are maintained post-implementation phase	Site leads, clinicians, organizational leaders, patients, caregivers	Survey, qualitative interviews
Fidelity	Degree to which sites adhere to their site-specific implementation plans	Site leads, clinicians	Survey, qualitative interviews
Cost analysis	Resources required to maintain the intervention and implementation supports	Site leads	Survey, qualitative interviews

### Statistical Analysis and Power Calculation

This primary analysis will be an intention-to-treat analysis with both unadjusted and adjusted analyses using generalized estimating equations. The primary intention-to-treat analysis will be applied to all enrolled hospitals and their outcomes, regardless of duration of intervention or implementation and actual adherence to the randomization at each site. Two-factor generalized estimating equations with a Poisson or negative distribution will be used to assess the effect of delivery mode (virtual vs in-person) and implementation support strategy (mentoring vs mentoring plus co-design), along with their interaction. Randomization “group 1” (deliver interventions virtually with mentoring plus co-design implementation support) will be compared to the remainder of the groups (Table 1). Covariates will include patient age, gender, and race, among others; hospital region; hospital type (academic vs community); setting (urban vs suburban vs rural); and hospital size. Models will also adjust for the baseline level of the primary outcomes at each individual hospital. Hospitals will be considered as a random intercept in a generalized linear mixed model, while within-hospital associations will be adjusted as clusters in a generalized estimating equation. We will also conduct pairwise comparisons among the four groups. For the primary effectiveness (30-day COPD-specific revisits) and the primary implementation outcome (reach of bundle), we will use 2-factor GEE with binomial distribution. A 2-sided type I error of 1% will be used for primary outcomes to account for multiple testing. Secondary outcomes, including other COPD-specific and all-cause 30-, 60-, and 90-day ED visits, readmissions, and revisits, will use the same methods as described above. These analyses will be exploratory and will not spend type I error of 5%. Time-to-event outcomes will be assessed via survival analysis with Cox proportional hazard regression models and Kaplan-Meier curves with the log-rank test. Tests of interaction to assess for any relationship between the intervention delivery (virtual versus in-person) and implementation support (mentoring only versus mentoring plus co-design) will also be performed. Given the testing of multiple hypotheses, a 2-sided *P* value of 1% will be considered significant. For analyses of secondary outcomes, a *P* value <5% will be considered significant regardless of type I error spending. For binary or count outcomes such as intervention provided (yes or no), the same statistical methods used in the primary analyses will be applied.

The sample size required for the trial is a minimum of 16 sites. For the primary effectiveness outcome of 30-day COPD-specific acute health care use, assuming a 30-day acute care revisit difference of 0.24 between virtual and in-person groups and a cluster size of 602, as was seen in pilot data [19,22,57], along with an intraclass correlation of 0.03, a total of 16 clusters and 4628 patients is needed to have 91% power to detect this difference. For the implementation outcomes of bundle reach, using a modified *z* test and assuming a 20% difference between receipt of interventions between arms and 90% power to detect a difference, 15 clusters with 4560 patients are needed. Both of these power calculations are at a 2-sided significance level of 1%.

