### Population and Setting

Hospitals interested in improving their COPD TOC programs for patients hospitalized with COPD will be recruited into the initial phase of the study. The sites will be primarily identified from the Hospital Medicine Reengineering Network (HOMERuN), a collaborative of hospitals and care teams aimed at creating and improving best practices via a learning network [13]. The HOMERuN sites are geographically diverse and include both academic and community hospitals. Additional sites will be recruited through the SHM [14]. The study aims to enroll at least 20 hospitals in the first phase (aim 1). To allow for sufficient power of the co-primary outcomes (see power calculation below) with up to 20% attrition in between this contextual assessment (aim 1) and randomization (aim 2), a minimum of 16 of the 20+ sites recruited into aim 1 sites are needed to participate in the trial (aims 2 and 3).

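### The 1% level for the two primary outcomes is not tied to a defined set of tests, and exploratory secondary results are called significant at an easier 5%

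*Protocol article*

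**What the plan says.** Everything here is in the protocol article, section Statistical Analysis and Power Calculation, unless noted.

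- **Outcomes.** There are two primary outcomes: "For the primary effectiveness (30-day COPD-specific revisits) and the primary implementation outcome (reach of bundle), we will use 2-factor GEE with binomial distribution". The section Population and Setting treats them as a pair: "To allow for sufficient power of the co-primary outcomes".
- **Level.** "A 2-sided type I error of 1% will be used for primary outcomes to account for multiple testing". The 1% threshold is repeated after the interaction tests, again with multiple hypotheses as the reason.
- **Contrasts.** The two-factor model is to "assess the effect of delivery mode (virtual vs in-person) and implementation support strategy (mentoring vs mentoring plus co-design), along with their interaction". Group 1 (virtual delivery, mentoring plus co-design) "will be compared to the remainder of the groups (Table 1"). Then: "We will also conduct pairwise comparisons among the four groups". Unadjusted and adjusted models both sit under the primary analysis. No order of testing is given and no contrast is named as primary.
- **Power.** Effectiveness is powered at 91% for virtual against in-person delivery (difference 0.24, intraclass correlation 0.03, 16 clusters, 4628 patients). Reach is powered at 90% for a 20% difference between arms that are not identified (15 clusters, 4560 patients). Both use a two-sided 1% level.
- **Secondary outcomes.** "These analyses will be exploratory and will not spend type I error of 5" per cent. A few sentences later, a secondary P value below 5% "will be considered significant regardless of type I error spending".

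**The concern.** A per-test level controls the overall error rate only over a stated set of tests. Here the level is offered as the multiplicity control, but the set is left open, and the tests listed outnumber what 1% can cover at an overall 5%. The text also points in different directions about what decides the trial. The effectiveness power calculation points to delivery mode, while the analysis paragraph gives group 1 against the remainder a sentence of its own. That sentence cites Table 1, which lists evidence for interventions and defines no groups, so it is unclear whether the other three groups are pooled or taken one by one.

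At stake is whether a P value below 1% on one of many contrasts can be presented as the trial's primary result, and whether the stated power applies to that contrast. The secondary rule adds a second problem: a result outside the error control may be called significant at a level five times as lenient as the primary one.

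**Working it through.** **Number of tests.** Per outcome there are 2 main effects + 1 interaction + 1 group 1 contrast (if the rest are pooled) + 6 pairwise (four groups, 4 × 3 / 2) = 10. Over two outcomes that is 20. Unadjusted and adjusted versions are not counted twice, because they are highly correlated.

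**What 1% covers.** 5% / 1% = 5, so by Bonferroni 1% per test guarantees 5% for at most five tests.

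**Familywise error with all nulls true.** Assume four arm estimates of equal variance, a normal approximation, and independent outcomes. The two main effects and the interaction are then mutually independent, so the error over k tests is 1 − 0.99^k:

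- Delivery mode only, k = 2: 1 − 0.99² = 2.0%
- Both main effects, k = 4: 1 − 0.99⁴ = 3.9%
- Main effects and interaction, k = 6: 1 − 0.99⁶ = 5.85%

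The group 1 and pairwise contrasts are correlated with these. Simulating 2,000,000 draws of four arm estimates, with rejection at |z| > 2.576, gives:

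- Factorial tests plus group 1 against the pooled rest: 3.58% per outcome; over two outcomes 1 − (1 − 0.0358)² = 7.0%
- All ten contrasts: 6.06% per outcome; over two outcomes 1 − (1 − 0.0606)² = 11.8%

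Treating all 20 tests as independent would give 18.2%, and the Bonferroni bound is 20%; both overstate the error.

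**The stated 91% power.** It cannot be reproduced, because no base rate is given. Read as an absolute difference of 0.24 in proportions with 8 against 8 clusters, power was at least 98.5% at every base rate tried. Read as event rates of 0.60 against 0.36 (an assumption), it was 89% to 91%, depending on whether cluster size is 4628 / 16 = 289 or the stated 602. The 91% is therefore taken as given below.

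**Whether that power carries over (illustration).** Assume 16 equal clusters, four per arm, and a normal approximation. The standardised effect for 8 against 8 is 2.576 + 1.341 = 3.917.

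- 4-against-4 comparison of the same size: the standard error rises by √2, so 3.917 / 1.414 = 2.77. Power = Φ(2.77 − 2.576) = 58%.
- Interaction (difference of differences) of the same size: the standard error doubles, so 3.917 / 2 = 1.96. Power = Φ(1.96 − 2.576) = 27%.

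With 20 equal clusters of the same size, 3.917 is multiplied by √(20/16) to 4.379, and the two figures become 70% and 35%.

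**Secondary rule.** The outcomes listed suggest 2 causes × 3 windows × 3 visit types − 1 primary = 17 (this count is mine; the article states none). At 5% on a single contrast, 17 × 0.05 = 0.85 false positives are expected; with three factorial tests each, 51 × 0.05 = 2.55.

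**The case against.** The strongest reply is that 1% is a sound choice for the tests that matter. It holds 5% for delivery mode alone or for both main effects, with room to spare, and adding the interaction exceeds 5% by less than one percentage point. The pairwise comparisons are introduced as an addition, which can be read as supplementary. No 5% familywise target is stated for the primary tests. All of this stands, and the fault is the undefined family, not the 1% level.

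A reader might infer that the primary error rate simply exceeds 5%. The article does not support that: it follows only if the interaction, or the full list, is confirmatory, which the text neither says nor rules out. A reader might also infer that virtual against in-person was the powered contrast for both outcomes. That holds for effectiveness only; for reach the arms are not identified. Nor can it be said that the fitted delivery coefficient will be a 4-against-4 simple effect, since that depends on a model coding the article does not give.

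Two further replies hold in part. A testing hierarchy is often left to the analysis plan, which is not shown. But the article itself gives the level, its purpose, the contrasts and both significance rules, and the objection is to how these fit together. A nominal 5% for exploratory outcomes is common practice and the article openly disclaims error control; the problem is calling such results significant.

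**Conclusion.** The point holds as a failure to define what the 1% level covers. Over the two primary outcomes the familywise error ranges from 2.0% to about 12%, depending on which listed contrasts are treated as confirmatory, and it passes 5% once the interaction joins both main effects. These figures assume equal-variance arms and independent outcomes, and the 5% yardstick is implied by the text, not stated for the primary tests.

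The stated power belongs to virtual against in-person for effectiveness and to an unnamed contrast for reach. It does not extend to the interaction, group 1 or pairwise tests. The 58% and 27% are illustrations that rest on 16 equal clusters and on the 91% being right; 16 is the planned minimum, and more sites would raise them.

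The secondary rule conflicts with itself on its face: the analyses lie outside the type I error, yet are judged significant at a more lenient level than the primary outcomes.

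**What to change.** - Name the marginal virtual against in-person effect as the primary contrast for effectiveness, at 1%.
- State which contrast reach was powered for. If the support-strategy main effect is also confirmatory, list it and keep the total within 5%; both main effects on both outcomes at 1% come to 4 × 1% = 4% by Bonferroni.
- Estimate the marginal effects from a main-effects model, or with effect coding if the interaction is in the model. Say whether the adjusted or the unadjusted model is primary.
- Make the interaction, group 1 against the rest and the pairwise comparisons secondary, reported with confidence intervals.
- Delete the rule that calls secondary P values below 5% significant. Report estimates, confidence intervals and nominal P values.
- State whether these choices were fixed before results were seen. The Results section reports that, as of August 2025, the baseline and implementation-phase analyses were nearly complete, so an undated choice could look post hoc.

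The cost is a change of wording in the protocol and analysis plan. The downside is that fewer results can be called significant.

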## Methods

### Study Design

This pragmatic, multisite study uses a hybrid type II effectiveness-implementation design to evaluate both clinical and implementation outcomes of COPD care transition programs across 20 diverse US hospital sites. After recruitment and enrollment, sites underwent a contextual assessment to develop site-specific implementation plans (published elsewhere) in aim 1 [11]. Participating hospitals will then be cluster-randomized to implement their intervention bundles using their site-specific implementation plans. Sites will be randomized to one of 4 intervention implementation groups, varying by program delivery method (in-person vs virtual) and implementation strategy (mentored implementation with or without co-design). Each site implements a tailored bundle of 2-3 evidence-based care transition interventions guided by the Society of Hospital Medicine (SHM)’s mentored implementation model (MIM) over a one-year period. Half of the sites also receive co-design support to actively engage end-users in shaping implementation approaches. The intervention groups are assessed through both quantitative outcomes, including acute care use, such as 30-day COPD-related revisits (primary effectiveness outcome) and bundle reach (primary implementation outcome). Deidentified patient-level data will be provided via Research Electronic Data Capture (REDCap; Vanderbilt University) and analyzed as below [12]. After one year of implementation, the project will enter the sustainment phase (aim 3), where ongoing effectiveness data and implementation data will be collected for an additional 2 years. Further, sustainment, fidelity, and cost will be evaluated through surveys and interviews. These post-implementation outcomes are measured over an additional 2-year follow-up period to assess the long-term sustainment and impact of implementation strategies and to inform future scale-up and dissemination (Figure 1). This study has been registered on ClinicalTrials.gov (NCT05568043).

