### Evidence-Based Interventions for TOC

During phase 1, individual sites select evidence-based interventions they wish to incorporate into their COPD TOC program (Table 1) [11]. Sites will then be randomized to deliver these COPD TOC programs either in person or virtually. All selected interventions are either part of standard clinical practice or supported by strong evidence for effectiveness. These interventions include, first, COPD action plans; these are structured tools that patients and health care providers review together to support patient self-management. Both the American Lung Association and the COPD Foundation have published free action plans that were available for use by sites [17,18]. Second, the interventions include gold standard inhaler education delivered using the “teach-to-goal” method [1,19,20]. Teach-to-goal adheres to the guideline-recommended “teach-back” technique [21] and is an iterative, patient-centered approach that ensures correct inhaler technique through cycles of teaching and testing (“teach-back”). It adapts to diverse learning needs and delivery methods and has demonstrated lasting improvements in both inhaler technique and health outcomes, making it a best-practice method in COPD inhaler education [19,22]. Third, medication reconciliation enhancements were also available for sites to adopt or expand upon, aiming to improve adherence and patient safety [23]. Fourth, post-discharge follow-up visits were used, whether in-person or virtual, as they have been associated with lower 90-day readmission rates; sites could opt to initiate new visit types or strengthen existing workflows and show rates [24,25]. Similarly, sites could choose to focus on patient navigation programs using community health workers, which draws on successful asthma models to support care continuity and address social determinants of health [26]. Fifth, smoking cessation assistance is provided, as it has proven associations with reduced mortality, slowed disease progression, and decreased acute care use in COPD patients [27,28]. Sixth, pulmonary rehabilitation is included in the interventions, as it is a well-established intervention that lowers readmission risks [29]. Sites had the option to launch a new program or work to enhance referrals and attendance in existing programs. Seventh, improved diagnostic testing through increased spirometry testing was also offered as an intervention option, addressing frequent underdiagnosis or misdiagnosis of COPD [30]. Eighth, sites had the option to update electronic health record order sets for COPD patients to streamline inpatient and outpatient COPD management by standardizing best practices for diagnosis and treatment. Consults for COPD care, general COPD education, and standardized note templates incorporating the above best practices were also interventions that could be included in site plans.

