### Outcomes

The primary effectiveness outcome for this study will be COPD-specific acute health care use, defined as a composite of all ED visits and hospitalizations within 30 days of index hospitalization for a COPD exacerbation. The primary implementation outcome will be reach, defined as the proportion of patients receiving their assigned TOC interventions (the whole bundle). Secondary effective outcomes will include additional acute care metrics related to COPD-specific and all-cause 30-, 60-, and 90-day revisits, ED visits, and readmissions. Secondary implementation outcomes include the reach of individual interventions within sites’ COPD TOC programs (ie, component-level reach).

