## Results

As of August 2025, 21 sites completed the contextual assessments and developed site-specific implementation plans. Publication of the qualitative data from this pre-implementation phase is anticipated in December 2025. Randomization of sites has been performed, and the sites that were randomized to co-design have completed 3 sessions. Baseline use data collection is complete. Use data collection for the implementation year is nearly complete. Use data collection for years 1 and 2 of the post-implementation phase is ongoing. Quantitative data analyses of the baseline and implementation phase reports are nearly complete, with anticipation of submission of the primary implementation phase manuscript in December 2025, pending submission of final implementation-phase data reports. Anticipate manuscript submission for the post-implementation sustainment analyses is anticipated for September 2026. Qualitative data collection for year 1 of the post-implementation phase is complete, and analysis is under way. Qualitative data collection for year 2 is being initiated as of August 2025.

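### Component-level reach is assigned the primary two-factor clustered model, but each component may be run at too few hospitals per arm to support it

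*Protocol article*

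**What the plan says.** Under Outcomes, the article lists the outcome: "Secondary implementation outcomes include the reach of individual interventions within" the sites' programs, which it calls component-level reach. Under Statistical Analysis and Power Calculation it gives the method: "For binary or count outcomes such as intervention provided (yes or no), the same statistical methods used in the primary analyses will be applied". For primary reach, that section specifies a two-factor binomial GEE. It also describes a delivery-by-support interaction, clustering on hospital, pairwise comparisons among the four arms, and adjusted as well as unadjusted analyses. Secondary effectiveness outcomes are called exploratory, but the section also lets secondary results be called significant at 5% regardless of type I error spending.

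The components differ from site to site. Study Design says "Each site implements a tailored bundle of 2-3 evidence-based care transition interventions", and Evidence-Based Interventions for TOC says that "individual sites select evidence-based interventions they wish to incorporate into their COPD TOC program". That section describes nine options and then adds three more: "Consults for COPD care, general COPD education, and standardized note templates incorporating the above best practices were also interventions that could be included". Table 1 adds remote monitoring.

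On the number of sites, the article says "across 20 diverse US hospital sites" (Study Design), "The sample size required for the trial is a minimum of 16 sites" (Statistical Analysis and Power Calculation) and "21 sites completed the contextual assessments" (Results). Allocation is 1:1:1:1 to four arms.

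**The concern.** Whole-bundle reach is defined at every hospital, so its model uses all 16-21 clusters. Reach of a named component is defined only at the hospitals that chose it. A model with an intercept, two factors and an interaction has four hospital-level parameters. It cannot be fitted if an arm is empty, and it leaves no information on between-hospital variation if each arm holds one hospital. A method that is workable for the primary outcome is therefore carried over to an outcome with a much smaller number of clusters.

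At stake are statements on whether virtual or in-person delivery, or co-design, improves reach of a particular component. Hospitals would use these results to decide how to deliver that component, and the plan lets them be called significant at 5%.

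**Working it through.** The plan gives no cluster count or power for component-level reach, so there is no figure of its own to reproduce here.

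**Menu.** Options counted in Evidence-Based Interventions for TOC: action plan, inhaler education, medication reconciliation, follow-up visit, patient navigation, smoking cessation, pulmonary rehabilitation, spirometry, order sets, consults, general education, note templates. That is 12, or 13 with remote monitoring from Table 1.

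**Hospitals per component** = sites × picks / options.

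- Lowest: 16 × 2 / 13 = 2.5, or 0.62 per arm.
- Central: 20 × 2.5 / 12 = 4.2, or 1.04 per arm.
- Highest: 21 × 3 / 12 = 5.25, or 1.31 per arm.
- All choices within Table 1's seven: 16 × 2 / 7 = 4.6 to 21 × 3 / 7 = 9, or 1.1 to 2.25 per arm.

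**Are all four arms covered?** Take 16 sites, four per arm, with a component shared by k of them at random.

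- k = 4: 4⁴ / C(16,4) = 256/1820 = 14%.
- k = 5: 1536/4368 = 35%.
- k = 6: 4480/8008 = 56%.

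Otherwise an arm is empty and the interaction is not estimable.

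Site choices were also simulated for 20 sites and 12 options under three assumed patterns: all options equally likely, popularity falling as 1/rank, and four popular options. About 72-78% of components had at least one empty arm, and about 90-99% had an arm with no hospital or one.

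**Where the model can be fitted.** With one hospital in each arm, four parameters reproduce four hospital proportions exactly. Each hospital's residuals sum to zero, so the sandwich variance is zero. A direct GEE fit gave a standard error of about 1e-16.

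False-positive rates were simulated with no true effect, using an uncorrected sandwich Wald test of the main effect with the interaction fitted. Assumptions: ICC 0.03 (stated for the effectiveness outcome; none is stated for reach), reach 50%, and 4628/16 = 289 patients per site.

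| Hospitals per arm | Median SE (log odds) | True SD | False positives at 5% | At 1% |
|---|---|---|---|---|
| 1 | 0 | 0.38 | 100% | 100% |
| 2 | 0.17 | 0.26 | 22-24% | 14% |
| 3 | 0.17 | 0.21 | 14% | 6% |
| 5 (all 20 sites) | 0.14 | 0.16 | 9% | 3% |

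At ICC 0.10 the 5% rates are similar: 100%, 23%, 13% and 11%. Pairwise arm contrasts reject 99%, 29% and 18% of the time at one, two and three hospitals per arm. Dropping the interaction avoids the zero standard error, but rejection is still 51% at one per arm and 19% at two.

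**Adjusted model.** The hospital-level terms number at least 10: four for intercept, factors and interaction, one for type, two for setting, and at least one each for region, size and baseline outcome (4 + 1 + 2 + 1 + 1 + 1). This assumes that every level is represented. A component run at nine or fewer hospitals cannot support them all.

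**The case against.** The strongest reply is that the article never says one model is fitted per component. The data list under Data Collection records completion of each site's interventions 1, 2 and 3, which would also suit a pooled patient-by-intervention analysis. That would keep every hospital, and the failure would not arise. Pooling rules are also detail that an article commonly leaves to a SAP. This stands in part: separate models are an inference. But the article does fix a rule, and an outcome worded as reach of individual interventions points to separate models. If pooling is meant, one sentence settles it.

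Second, the sites' choices are not reported. A reader might infer that most components actually run at one hospital per arm. The documents do not support that: about one per arm is an average over the menu. Choices concentrated on a few popular components would leave two or more per arm, where the test is too liberal but does not collapse.

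Third, a reader might infer that component results would come out significant by construction. That needs exactly one hospital in every arm with the interaction fitted (14% when four of 16 sites share a component) or the pairwise contrasts. An empty arm is the commoner failure, and an analyst would see it.

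Fourth, the article names no variance estimator. A small-sample correction would reduce the inflation at two or three hospitals per arm. Neither it nor the random-intercept model that the article also mentions would rescue an empty arm or one hospital per arm.

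**Conclusion.** The concern holds in limited form. Read naturally, the plan applies a two-factor, hospital-clustered interaction model to outcomes that on average only about 2.5-5 hospitals contribute to (4.6-9 if choices stayed within Table 1). Many components would then have an arm with no hospital or one, and the model would often not be estimable. Where it could be fitted without a small-sample correction, its error bars would be too small, by the amounts tabulated.

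This rests on separate per-component models, on assumed choice patterns, and on the simulation inputs stated above. It concerns a secondary outcome; neither primary conclusion nor the sample size is affected. It should still be corrected, because the plan lets these results be called significant at 5%.

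**What to change.** State that component-level reach is tested in one pooled analysis over all randomised hospitals. Use patient-by-component rows with component type as a fixed effect, since the mix of components may differ between arms. Cluster on hospital, with a small-sample correction or degrees of freedom based on the number of sites. The correction is needed even here: with all 20 sites, the uncorrected test rejects about 9% of the time at nominal 5%.

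Report reach of each named component by hospital and arm descriptively, without P values, at least where hospitals per arm are few, and state that minimum number in advance.

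The cost is a few lines of analysis-plan wording and the loss of per-component P values, which would not be valid for sparse components. The pooled test answers a question averaged over components, not one about a particular component. The Results section says quantitative analyses of the implementation phase are nearly complete, so the wording should be settled before component-level results are reported.
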